#### Exploratory measures

2.10.5

The RE-AIM evaluation framework [23] is used to explore the potential population-level impact and generalizability of the intervention in real-world clinical settings. To Measure reach, patient participation rates will be calculated using the registry lists as the denominator and representativeness of enrolled participants versus non-participants are compared based on baseline BMI, age, rurality, and sex. Adoption, implementation, and maintenance at the clinic level will be explored through mixed methods including study-specific surveys and focus groups with participating PCPs. To explore the relative importance of place and context for impacting outcomes, multiple participant-level and spatial-level measures will be collected. Participant-level contextual measures will be collected at baseline. Spatial level measures will be captured from available public data based on participants’ home addresses and include social disadvantage indicators from the American Community Survey [61], food dessert indicators from the USDA Food Access Research Atlas [62], and county-level prevalence of obesity, physical inactivity based on County Health Rankings [63].

### Data management and statistical analysis

2.11

#### Sample size

2.11.1

As little as 3–5 % weight loss is clinically meaningful [64]. In RE-POWER, a clinic group-based intervention showed 4.3 % loss at 24 months, and we expect a larger mean effect from the additional medical management component. To determine sample size, we set the type I error at 0.05, intraclass correlation coefficient at 0.02 as was observed in RE-POWER, and 35 participants per clinic. With 16 clinics, the trial will have 85 % power to detect a net between-group treatment effect of 3 % (SD = 8).

#### Missing data

2.11.2

Based on our prior history using a similar retention plan, we expect to retain at least 85 % of participants at the final 18-month data collection visit, with a goal of 90 %. We will evaluate the missing data pattern for differential loss to follow-up based on treatment arm. In the absence of differential loss to follow-up, the primary analysis described above will use restricted maximum likelihood, and no participants will be deleted from analysis due to missing data. We will conduct a sensitivity analysis to evaluate the sensitivity of the results including only participants who have no missing data.

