*Local Care.* Local Care consists of quarterly PCP visits that follow a 5A's (Assess; Advise; Agree; Assist; Arrange) model, consistent with practice guidelines and the Medical Intensive Behavior Therapy (IBT) benefit [34,35]. Standardized participant hand-outs will be provided to address core elements of obesity treatment guidelines including nutrition and physical activity goal setting and tracking. Local Care handouts cover the same nutrition and physical activity guidelines as the lifestyle intervention in the Team Care arm. Local Care participants also receive a Fitbit and smart scale and will be instructed to use the MyNetDiary app. In addition, the study team assists Local Care clinics in developing a hand-out of local community resources to share with participants.

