#### Statistical analysis for primary aim

2.11.3

Percent weight loss at 18 months will be compared between the treatments. Hierarchical linear mixed models will be used to examine the group differences, accounting for the correlation between participants from the same clinic and for the correlation of measures from the same participants.

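### Use of REML for the primary analysis is tied to equal loss by arm, which is the wrong criterion, and the only missing-data sensitivity analysis cannot probe informative dropout

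*Protocol article*

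**What the plan says.** Section 2.11.2 of the protocol article sets out four things in order.

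- Expected retention: "we expect to retain at least 85 % of participants at the final 18-month data collection visit, with a goal of 90" %. That leaves 10–15% missing at month 18, or 56 to 84 of 560 participants.
- A check: "We will evaluate the missing data pattern for differential loss to follow-up based on treatment arm". No threshold or test is given.
- A rule that follows from the check: "In the absence of differential loss to follow-up, the primary analysis described above will use restricted maximum likelihood, and no participants will be deleted" for missing data. Nothing is said about the case where loss is found to differ.
- One sensitivity analysis for missing data: "We will conduct a sensitivity analysis to evaluate the sensitivity of the results including only participants who have no missing data".

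Section 2.11.3 defines the primary model as a hierarchical linear mixed model for percent weight loss at 18 months, "accounting for the correlation between participants from the same clinic and for the correlation of measures from the same participants". The other sensitivity analyses exclude recipients of pharmacotherapy or surgery (section 2.11.4) or adjust for imbalanced baseline variables (section 2.11.5). Neither concerns missing data.

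**The concern.** The rule treats similar dropout in the two arms as the licence for REML. A likelihood-based mixed model needs something else: that missingness depends only on what is observed and modelled, such as arm and earlier weights (missing at random, MAR). Equal loss by arm is neither necessary nor sufficient for that. The rule can therefore set aside a valid analysis and clear a biased one.

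The empty branch is a realistic one. Section 2.8 gives Team Care weekly, then bi-weekly, then monthly group sessions plus coach pre-visits, while Local Care has quarterly visits. With contact that different, unequal loss is plausible, and the estimation method would then be settled after loss by arm is known.

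The completers-only run does not fill the gap. Unlike REML, it discards the earlier weights of those who leave. It therefore needs a stronger assumption about dropout, and its agreement with the primary result says nothing about dropout that depends on unseen weight regain. At stake is how far the 18-month difference can be trusted if those who leave differ between arms.

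**Working it through.** **The plan's own figure.** Section 2.11.1 gives 16 clinics (8 per arm), m = 35 per clinic, SD 8, ICC 0.02, alpha 0.05 (two-sided assumed), a difference of 3 points and 85% power. Design effect = 1 + (m − 1) × 0.02; SE = 8 × √(2 × design effect / (8m)); power from a noncentral t with 14 df (16 clinics minus 2).

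- m = 35: design effect 1.68, power 88.9% (92.8% by normal approximation).
- m = 31.5 (10% loss): design effect 1.61, power 86.9%.
- m = 29.75 (15% loss): design effect 1.575, power 85.8%.

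The stated 85% is reproduced within 2 points once 10–15% loss is allowed for. This point leaves the power figure unchanged; the standard errors are used in step 2.

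**Step 1. Is equal loss by arm the right criterion?** The check is a large-sample simulation with 400,000 participants per arm and no clinic effect. From the protocol article: 18-month SD 8 and a difference of 3.0. Assumed: mean changes of −7 and −6 points at months 6 and 18 in Team Care, and −2 and −3 in Local Care; 6-month SD 6; correlation 0.65 between the visits.

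Dropout after month 6 follows logit P = a + b × (deviation from the arm mean). Informative loss has b = 0.15 per point, so poorer weight loss means more dropout; random loss has b = 0. The constant a is set to give the stated loss. Under MAR the deviation is that of the observed 6-month value. Under MNAR (missing not at random) it is that of the unobserved 18-month value.

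The likelihood estimate regresses month 18 on month 6 within each arm and predicts at the full-arm month-6 mean. The completers estimate is the plain difference in means.

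| Loss, Team / Local | Mechanism | Likelihood | Completers |
|---|---|---|---|
| 10% / 20% | MAR, both arms | 3.0 | 2.6 |
| 20% / 10% | MAR, both arms | 3.0 | 3.4 |
| 15% / 15% | MAR in Team Care, random in Local Care | 3.0 | 3.6 |
| 15% / 15% | MNAR in Team Care, random in Local Care | 3.7 | 4.2 |
| 15% / 15% | MNAR, same in both arms | 3.0 | 3.0 |

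Rows 1 and 2: loss is differential and the likelihood analysis is unbiased. Row 4: loss is equal and it is biased. Row 5: with the same mechanism and rate in both arms, the biases cancel. Wherever either estimate is off, completers-only is further from 3.0.

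**Step 2. How large could the effect be at the planned loss?** With equal loss d in each arm, bias in the difference = d × (shift in Team Care dropouts − shift in Local Care dropouts). A shift is how far dropouts' true mean departs from what MAR predicts. Assume an observed difference of exactly 3.0.

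- 15% loss: SE = 8 × √(2 × 1.575 / 238) = 0.92; critical difference = 2.145 × 0.92 = 1.97. Significance is lost when the shifts differ by (3.0 − 1.97) / 0.15, about 6.8 points. The effect is erased at 3.0 / 0.15 = 20 points.
- 10% loss: SE = 0.90, critical difference 1.94. Significance is lost at (3.0 − 1.94) / 0.10, about 10.6 points.
- Return to baseline for all dropouts at 15% loss in each arm, taking 3.0 as the difference among those observed: 0.85 × 3.0 = 2.55, still above 1.97 if the same SE is used as a rough guide.

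**The case against.** The strongest reply is that section 2.11.3 defines the mixed model without any condition; section 2.11.2 conditions only REML and the no-deletion statement. A reader might infer that no primary analysis exists if loss differs, or that REML is then forbidden. The text supports neither. What is missing is the estimation and missing-data approach for one branch.

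A reader might also infer that the plan gives no protection against dropout. That is too strong: REML protects against loss explained by arm and observed weights, as the MAR rows show. The unprotected case is informative dropout, and even there a mechanism common to both arms leaves the difference intact.

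Three further replies stand.

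- It is tempting to call the check an underpowered significance test. The protocol article names no test, and evaluating a pattern could include looking at who is lost, so nothing here rests on that.
- The no-deletion statement is usual shorthand for no listwise deletion. It fails only for participants with no follow-up weight at all, whose number is not given, so this is minor.
- The mere absence of an MNAR analysis could be left to an analysis plan that is not shown.

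None of this answers the remaining point. The wrong criterion, the unstated branch and the choice of completers-only are all in the text, and an analysis plan that followed it would inherit them.

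**Conclusion.** The point holds as a should-fix. Loss rates by arm are the wrong basis for deciding whether to use REML, the differential-loss branch has no stated approach, and completers-only cannot test for informative dropout.

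The simulated sizes (completers-only at 2.6 to 3.6 against 3.0 under MAR; 4.2 against 3.7 with equal 15% loss that is MNAR in Team Care only) depend on the assumed 6-month SD, correlation and dropout slope. They show direction and order of magnitude and do not forecast this trial. The simulation uses two visits; month-12 weights on people lost late would let REML recover more.

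At 10–15% loss the likely impact on the primary conclusion is moderate. With an observed 3.0, dropouts' shifts would have to differ between arms by about 7 to 11 points to lose significance. The conclusion that the criterion is wrong does not depend on these inputs.

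**What to change.** In section 2.11.2, delete the conditional clause, so that the mixed model fitted by REML to all observed follow-up weights is the primary analysis whatever the loss by arm. Report loss by arm, and the characteristics of those lost, descriptively.

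Replace or supplement the completers-only run with a sensitivity analysis for informative dropout that also includes participants with no follow-up weight. An arm-specific delta or tipping-point analysis addresses the case where the mechanism differs between arms; return-to-baseline imputation is a simpler alternative.

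This should be settled before outcome data are examined. The cost is wording and a few extra model runs, with no change to sample size or conduct. Modelling log weight, or substituting synced smart-scale readings for missed visits, is optional and not needed to resolve the point.

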#### Statistical analysis for primary aim

2.11.3

Percent weight loss at 18 months will be compared between the treatments. Hierarchical linear mixed models will be used to examine the group differences, accounting for the correlation between participants from the same clinic and for the correlation of measures from the same participants.

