### Primary care practice and provider recruitment

2.3

Clinics intend to be recruited through connections facilitated by the study team and Community Advisory Board. Rural primary care practices that predominately or exclusively serve rural residents in Kansas will be enrolled. A total of sixteen clinics in 4 cohorts of 4, with different degrees of rurality and region, are planned to be recruited.

All practices will be required to identify a PCP champion and a primary administrative contact. Practices must be able to provide a registry of 300–400 patients with a BMI ≥30 kg/m2 in accordance with their practice's HIPAA policies. During the practice recruitment process, the PCP champion will approach other providers at the practice to offer the opportunity to participate in the study. Participating providers must be willing to provide enrolled patients at least quarterly visits for weight management, and if randomized to Team Care, to engage with the lifestyle coaches via telemedicine during those quarterly clinic visits.

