### Cluster randomization

2.4

Primary care practices will be randomly allocated in equal proportions (1:1) to each of the two study arms (Team Care, Local Care) in pairs after the target number of participants at the sites have been screened eligible and eligible participants have completed their initial baseline surveys. Eight practices are expected to enroll into each arm. Participants remain blinded to randomization until fully enrolled in the study. Practice staff will be notified during final participant enrollment steps to allow for sufficient lead time for practice staff to schedule the first quarterly clinic visits approximate in time to the baseline weight measurement.

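### Practices enter in four cohorts and are randomised in pairs, but the primary model as described has no cohort term; if cohorts differ, the arm test is conservative and loses power

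*Protocol article*

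**What the plan says.** Section 2.3 (Primary care practice and provider recruitment) plans "A total of sixteen clinics in 4 cohorts of 4", differing in rurality and region. Section 2.4 (Cluster randomization) allocates practices "1:1) to each of the two study arms (Team Care, Local Care) in pairs", once enough participants at the sites have been screened and have completed their first surveys. Section 2.9 (PCP training) gives the initial training separately to each cohort.

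Section 2.11.3 (Statistical analysis for primary aim) specifies hierarchical linear mixed models "accounting for the correlation between participants from the same clinic and for the correlation of measures from the same participants". Neither cohort nor pair is named. Section 2.11.4 uses a similar strategy for the secondary outcomes. Section 2.11.5 (Potential confounders) places covariate adjustment in sensitivity analyses and selects baseline variables by their standardised difference between arms.

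The sample size (section 2.11.1) rests on an "intraclass correlation coefficient at 0.02 as was observed in RE-POWER, and 35 participants per clinic", with no separate cohort component.

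**The concern.** Cohort groups practices by recruitment and by training. If each cohort holds two randomised pairs, then each has two practices per arm, and differences between cohorts cancel from the arm comparison. They do not cancel from the residual variation between practices that the model uses as its yardstick. A model without cohort therefore overstates the standard error of the arm effect. The test rejects too rarely under the null and has less power under the alternative.

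This matters here because there are only sixteen practices and the planned power has little to spare. The adjustment rule in section 2.11.5 does not help: it looks for imbalance between arms, and a factor balanced by design shows none, however strongly it predicts weight loss.

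**Working it through.** **Inputs.** From section 2.11.1: effect 3 percentage points, SD 8, ICC 0.02, 16 clinics, 35 participants per clinic, type I error 0.05 (taken as two-sided; the article does not say). From section 2.11.2: at least 85% retained at 18 months, so 35 × 0.85 = 29.75 per clinic. From section 2.4: 8 practices per arm. The cohort variance is not given and is assumed over a range.

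**Step 1: the plan's own power.** Total variance is 8² = 64, so the between-clinic variance is 0.02 × 64 = 1.28 and the within-clinic variance is 62.72. The variance of a clinic mean is 1.28 + 62.72/29.75 = 3.388. Then

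SE = √(2 × 3.388 / 8) = 0.920, and the noncentrality is 3 / 0.920 = 3.26.

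A t test on 16 − 2 = 14 df gives 85.8%. This reproduces the stated 85%, with no cohort or pair term. With no loss to follow-up (35 per clinic) the same formula gives 88.9%.

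**Step 2: cost of a term that explains nothing.** With the same noncentrality:
- cohort as a fixed effect, 14 − 3 = 11 df: 84.3%
- eight pairs as fixed effects, 14 − 7 = 7 df: 79.8%

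**Step 3: how omission inflates the standard error.** Let v be the variance of a clinic mean within a cohort (3.388) and c the cohort variance. With four cohorts of four, balanced by arm, the unadjusted residual mean square has expectation (14v + 12c)/14 = v + 0.857c. At c = 1 this is 3.388 + 0.857 = 4.245, so the reported SE is too large by a factor of about √(4.245/3.388) = 1.12. The true sampling error of the arm difference is unchanged.

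**Step 4: cohort variance on top of the ICC of 0.02.** Simulation of 16 clinic means, two practices per arm in each cohort, 85% retention:

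| Assumed cohort SD (points) | Power, no cohort term | Power, cohort fixed effect | Type I error, no cohort term |
|---|---|---|---|
| 0 | 86% | 84% | 5.0% |
| 0.5 | 84% | 84% | 4.5% |
| 1.0 | 79% | 84% | 3.3% |
| 1.5 | 71% | 84% | 2.2% |

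The cohort-adjusted test holds its type I error at 5% throughout. Fitting pairs gives about 80% in every row.

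**Step 5: cohort variance already inside the ICC of 0.02.** Here the total between-clinic variance stays at 1.28 and cohort makes up a share of it:

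| Share of the 1.28 due to cohort | Power, no cohort term | Power, cohort fixed effect |
|---|---|---|
| None | 85.8% | 84.3% |
| Half | 88.4% | 90.9% |
| All | 90.9% | 96.3% |

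Unadjusted power does not fall below the planned 85%. The gain from adjustment is 2.5 points at half and 5.4 points at all. At one quarter it is under 1 point.

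**The case against.** The strongest reply is that section 2.11.3 is two sentences in a condensed article. It describes the correlation structure and lists no fixed effects at all, so a cohort term would be compatible with it and may stand in a fuller plan. This holds in part. A reader might infer that the plan has decided to leave cohort out, and the article does not say that. What it does say about adjustment, in section 2.11.5, confines it to sensitivity analyses and uses a selection rule that would pass over cohort. That much is on the page.

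The second reply concerns the design. A reader might take it as stated that cohorts enter one after another and that pairs lie within cohorts. Neither is stated. Randomisation in pairs as sites become ready, and training held by cohort, make both very likely. The article also gives no evidence that use of weight-loss medication changes between cohorts.

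The third reply is that the loss of power is assumed. This also stands: no cohort variance is given. An SD of 1.5 points is a variance of 2.25, against a whole planned between-clinic variance of 1.28. At an added SD of about 0.5 or less, adjustment brings no net gain.

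Finally, the pair is the only grouping that the article ties to randomisation, yet the remedy is cohort. The reason is degrees of freedom: seven are left after fitting pairs and eleven after cohort. Cohort removes variation shared by four practices at a small price.

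**Conclusion.** The point holds as a conditional matter of efficiency. The primary analysis as described leaves any difference between cohorts in the between-clinic variance, and the stated adjustment rule would not remove it. If such differences come on top of the ICC of 0.02, power falls from about 86% to 79% at a cohort SD of 1.0 point and to 71% at 1.5, where a cohort term would hold it at about 84%. If they are already part of the 0.02, the planned power is met either way and the term is a possible gain.

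A reader might go further and infer that the trial is underpowered or its result biased. The documents support neither. The stated 85% reproduces, balance by design keeps the estimate unbiased, and type I error stays at or below 5%. The calculation assumes two practices per arm in each cohort, equal clinic sizes, a two-sided test on clinic-level degrees of freedom and 85% retention.

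**What to change.** State whether pairs are formed within cohorts. If they are, prespecify cohort (four levels) as a fixed effect in the primary model and in the secondary arm comparisons. Test the arm effect in the primary linear model on clinic-level degrees of freedom, 16 − 2 − 3 = 11. Do not fit eight pair indicators: they leave 7 df and about 80% power when pairs carry no information of their own.

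This is one model term, to be fixed before outcome data are seen by arm. If cohorts do not differ at all, it costs 85.8 − 84.3 = 1.5 points of power. If a fuller analysis plan already contains the term, one sentence saying so settles the point.

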#### Secondary and exploratory aims

2.11.4

Each secondary outcome at 18 months will be compared across arms using separate hierarchical linear mixed model in a similar strategy as the primary aim, except for the proportion achieving clinical cut points of 5 % and 10 % weight loss. These will be compared across arms usings generalized linear mixed models.

To evaluate the impact of pharmacotherapy and bariatric surgery on the between-arm difference in % weight loss, we will add receipt of pharmacotherapy and bariatric surgery to the primary aim to estimate the influence of each on % weight loss beyond other aspects of the intervention. We will use generalized linear mixed models to estimate the proportion who begin pharmacotherapy or undergo bariatric surgery, adjusting for baseline covariates (age, sex, race, education, BMI, insurance, co-morbid conditions), and then multiply the proportion by the effect on % weight loss to calculate impact for each arm, using bootstrapping to derive confidence intervals. We will also conduct a sensitivity analysis on the primary analysis, excluding participants who receive one or both.

Mental health, pain, sleep quality and other medical treatment process outcomes will be compared across treatment arms at 6 and 18 months using separate mixed models in a similar strategy as the primary and secondary aims. Each RE-AIM measure will be compared across treatment arms using descriptive statistics.

To explore the associations between participant-level and tract/county-level contextual measures and % weight loss, we will use hierarchical linear models including variables with the strongest bivariate associations (p < 0.10).

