#### Potential confounders

2.11.5

For all statistical models, sensitivity analyses will be performed using the models above but also adjusting for potential confounders among the baseline variables identified as varying across arms based on their standardized differences.

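### The baseline covariates are assigned to the model for who starts medication or surgery, but none is named for the model of what receipt does to weight, where confounding enters

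*Protocol article*

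**What the plan says.** Section 2.11.4 of the protocol article (Secondary and exploratory aims) sets out a three-step calculation.

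1. Effect of receipt: "we will add receipt of pharmacotherapy and bariatric surgery to the primary aim to estimate the influence of each on % weight loss".
2. Uptake: "We will use generalized linear mixed models to estimate the proportion who begin pharmacotherapy or undergo bariatric surgery". The list of seven baseline covariates belongs to this sentence.
3. Product: the proportion is multiplied by the effect for each arm, with bootstrap intervals. Steps 2 and 3 are joined in the words "adjusting for baseline covariates (age, sex, race, education, BMI, insurance, co-morbid conditions), and then multiply the proportion by the effect on % weight loss".

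The primary model that step 1 builds on is in section 2.11.3. It is described as a hierarchical linear mixed model "accounting for the correlation between participants from the same clinic and for the correlation of measures from the same participants"; no baseline covariate is named.

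Two other provisions bear on this. Section 2.11.5 adds, for all models, a sensitivity analysis "adjusting for potential confounders among the baseline variables identified as varying across arms based on their standardized differences". Section 2.11.4 also says: "We will also conduct a sensitivity analysis on the primary analysis, excluding participants who receive one or both".

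Section 2.2 places the impact of medication and surgery on the between-arm difference among the tertiary aims.

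**The concern.** Clinics are randomised; receipt of medication or surgery is not. Table 1 has the PCP prescribe when indicated and refer for surgery as needed, and section 2.8 has patient preferences discussed at team visits. BMI, co-morbidity, insurance and age can plausibly influence who receives treatment, and several of them can also predict weight loss. The coefficient for receipt is therefore an observational estimate, and it is the factor of the product that most needs baseline adjustment. As written, the adjustment set is attached only to the other factor.

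At stake is the answer to the tertiary question of how much of the difference between arms runs through medication and surgery. If one receipt coefficient serves both arms, the between-arm impact is that coefficient times the difference in uptake, so a given percentage error in the coefficient becomes the same percentage error in the impact. The bootstrap reflects sampling error only and would place an interval around the confounded product.

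**Working it through.** **What can be reproduced.** The article gives no uptake rate, receipt effect or covariate strength, so this analysis has no stated figure to reproduce. The planned power concerns the primary comparison and plays no part here. Only the layout of the illustration comes from the document: 16 clinics and SD 8 from section 2.11.1, together with "we set the type I error at 0.05, intraclass correlation coefficient at 0.02 as was observed in RE-POWER, and 35 participants per clinic". All other inputs below are assumptions.

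**Does another provision supply the missing adjustment?**

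- Section 2.11.5 selects "potential confounders among the baseline variables identified as varying across arms based on their standardized differences". A variable can be balanced between arms and still differ strongly between recipients and non-recipients, in which case this rule does not pick it. It is also only a sensitivity analysis.
- Excluding recipients conditions on a post-randomisation choice and gives no estimate of the receipt effect.

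**Hand calculation with one binary confounder D.** Bias in the receipt effect = g × [P(D | receipt) − P(D | no receipt)], where g is the effect of D on % weight loss. Prevalence of D is assumed to be 0.30 and the true receipt effect 8 points.

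- Uptake 0.40 with D and 0.15 without, g = −2. Overall uptake = 0.30 × 0.40 + 0.70 × 0.15 = 0.225. P(D | receipt) = 0.120/0.225 = 0.533; P(D | no receipt) = 0.180/0.775 = 0.232. Bias = −2 × 0.301 = −0.60, so 8 is estimated as 7.4.
- Uptake 0.50 and 0.10, g = −3. Overall uptake = 0.15 + 0.07 = 0.22. P(D | receipt) = 0.15/0.22 = 0.682; P(D | no receipt) = 0.15/0.78 = 0.192. Bias = −3 × 0.490 = −1.47, so 8 is estimated as 6.5.

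**Simulation.** 16 clinics of 35, 400 replicates per setting, one standard-normal composite covariate, true receipt effect 8, direct arm effect 3, residual SD 8, clinic SD √0.02 × 8 = 1.13. Ordinary least squares and logistic fits stood in for the mixed models. Uptake was about 28–31% in Team Care and 19–23% in Local Care.

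| Covariate log-odds on uptake, per SD | Covariate effect on % loss, per SD | Receipt effect, covariate omitted | Receipt effect, covariate included |
|---|---|---|---|
| 0 | −2, 0 or +2 | 8.0 | 8.0 |
| 0.5 | −2 | 7.1 | 8.0 |
| 0.5 | 0 | 8.0 | 8.0 |
| 0.5 | +2 | 9.0 | 8.1 |
| 1.0 | −2 | 6.3 | 8.0 |
| 1.0 | 0 | 8.0 | 8.0 |
| 1.0 | +2 | 9.6 | 8.0 |

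Bias appears only when the covariate is related to both uptake and weight loss, and it can go either way.

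**Carry-through to the product.** In the log-odds 1.0 settings, with observed uptake in the product, the between-arm impact was 0.76 unadjusted against 0.63 adjusted (outcome effect +2), and 0.50 against 0.63 (outcome effect −2). The ratios 0.76/0.63 ≈ 1.2 and 0.50/0.63 ≈ 0.8 match those of the effects: 9.6/8.0 = 1.2 and 6.3/8.0 ≈ 0.8.

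**The uptake factor.** In the same settings, observed uptake was 0.31 and 0.23. The covariate-adjusted proportion averaged over the sample was also 0.31 and 0.23. Read at mean covariates it was 0.28 and 0.19. Adjustment itself therefore does no harm; only the way the proportion is read off matters, and the article does not say which way is meant.

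**The case against.** A reader might infer that both factors of the product are biased, because a covariate-adjusted proportion differs from actual uptake. The document does not support that. Averaged over the sample, the adjusted proportion equals observed uptake; it falls below it only if read at mean covariates, which the article never says. Nor is adjusting uptake misplaced. With eight clinics per arm, chance differences in case mix can shift uptake, and adjustment helps a fair comparison of arms.

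It can also be said that section 2.11.3 is a short condensation, and that naming no covariates is not the same as excluding them. That has some force, since a fuller list may exist in the analysis plan. But section 2.11.4 does write out an adjustment set and attaches it to one factor only. That is a stated placement, not just omitted detail.

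The illustrative biases are modest beside sampling error. With 22% uptake among 560 participants and SD 8, the standard error of the receipt effect is about 8 × √(1/123 + 1/437) = 0.82, ignoring clustering and dropout, so the 95% half-width is 1.60. Biases of 0.60 and 1.47 lie inside it. This limits the importance of the point but does not remove it, because an interval centred on a confounded value under-covers.

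Finally, the simulation recovers 8 because the covariate adjusted for was the only confounder. In the trial, early weight response could influence later prescribing during 18 months of quarterly visits, and baseline covariates cannot remove that. This objection stands in full.

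**Conclusion.** The point holds for the effect of receipt. Followed as written, the plan takes a non-randomised effect from a model with no named baseline covariates and multiplies it into the impact figure, while the covariates it does name go only to the uptake model. Neither section 2.11.5 nor the exclusion of recipients repairs this.

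Size and direction cannot be taken from the document. On the assumed inputs, a true effect of 8 points is estimated at 6.3 to 9.6 without adjustment and 8.0 to 8.1 with it, and at 8 either way when the covariate is unrelated to uptake or to weight loss. For the uptake proportion, all that can be said is that the way it is averaged is not stated.

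The consequence is confined to one tertiary analysis. The primary comparison of arms does not use receipt and is unaffected.

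**What to change.** In section 2.11.4:

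- Include the same seven pre-specified baseline covariates in the % weight-loss model that estimates the effect of receipt, with categorical ones entered as indicators.
- State that the uptake proportion used in the product is averaged over the covariate distribution (standardised), not read at mean covariates.
- Report the impact estimate as observational, noting that confounding by early weight response during follow-up remains.

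The cost is a change of wording and a few more terms in one tertiary model. The covariates are already named, and Table 4 schedules demographics and medical history at baseline. Residual confounding is reduced, not eliminated.
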